### **3 Ethics**

#### **3.1 Independent Ethics Committee (IEC) and Regulatory Authorities**

Before this study will be conducted, the protocol, the proposed subject information and consent form as well as other study-specific documents will be submitted to a properly constituted Independent Ethics Committee (IEC) and regulatory authorities (Swissmedic/BAG) in agreement with local legal requirements, for formal approval. Any amendment to the protocol must be approved by these institutions.

The decision of the IEC and Swissmedic concerning the conduct of the study will be made in writing to the Sponsor-Investigator before commencement of this study.

#### **3.2 Ethical Conduct of the Study**

The study will be carried out in accordance with principles enunciated in the current version of the Declaration of Helsinki, the guidelines of Good Clinical Practice (GCP) issued by ICH, and Swiss regulatory authority's requirements.

IEC and regulatory authority will receive annual safety and interim reports and be informed about study stop/ end in agreement with local requirements.

#### **3.3 Subject Information and Informed Consent**

The investigator must explain to each subject the nature of the study, its purpose, the procedures involved, the expected duration, the potential risks and benefits and any discomfort it may entail. Each subject must be informed that the participation in the study is voluntary and that he/she may withdraw from the study at any time and that withdrawal of consent will not affect his/her subsequent medical treatment.

The subject must be informed that his/her medical records may be examined by authorized individuals other than their treating physician.

All subjects for this study will be provided a subject information sheet and a consent form describing this study and providing sufficient information for subjects to make an informed decision about their participation in this study.

The subject information sheet and the consent form will be submitted with the protocol for review and approval for the study by the IEC and by Swissmedic. The formal consent of a subject, using the approved consent form, must be obtained before that subject is submitted to any study procedure.

The subject should read and consider the statement before signing and dating the informed consent form, and should be given a copy of the signed document. The consent form must also be signed and dated by the investigator (or his designee) and it will be retained as part of the study records.

## 4 INTRODUCTION

This document is a protocol for a human research study.

### 4.1 Background and Rationale

Chronic hepatitis C virus (HCV) is a major cause of morbidity and mortality worldwide with an estimated number of 180 million infected patients. HCV infection causes around 376'000 deaths per year due to complications like hepatocellular carcinoma (HCC) and endstage liver disease (1). In Switzerland, 50'000-70'000 individuals are HCV infected (2). HCV-HIV co-infection is reported in approximately 30% of all Swiss HIV Cohort Study (SHCS) participants (3). In 2010, almost 100 liver transplantations have been performed, 25% of them because of HCV-related endstage liver disease (4).

Until 2012 the current standard treatment of patients with chronic hepatitis C was a 24 to 72 weeks therapy with pegylated interferon- $\alpha$  and ribavirin (PR). Response to the treatment with PR depends on the HCV-genotype, HCV-HIV co-infection, baseline hepatitis C viral load, interleukin 28 B genotype, sex and stage of fibrosis (5). Sustained virological response (SVR) after treatment with PR can be achieved in 30% to 80% in treatment-naïve patients, depending on host and viral characteristics.

In 2012, the protease-inhibitors (PI's) telaprevir and boceprevir as first directly acting HCV drugs have been approved by Swissmedic for hepatitis C mono-infected and HCV-HIV-co-infected individuals. However, therapy success is strongly limited in null-responders (NR) to previous PR. NR is defined as a reduction of  $< 2\log_{10}$  in HCV RNA after 12 weeks of therapy. Of note, in patients with previous failure to PR, TT is in fact a mono-therapy with a high risk of rapid development of resistance against the PI's. Treatment of HCV-HIV co-infected individuals with the new PI's is accompanied by additional challenges including drug-drug interactions, toxicity, and a high pill burden which impedes drug adherence.

Only preliminary data exist regarding the efficacy of a triple therapy (TT) with telaprevir or boceprevir and PR in co-infected patients. In a phase 2a study 59 HCV-HIV co-infected individuals with HCV genotype 1A were randomized to receive a TT for 12 weeks with telaprevir and PR followed by 36 weeks of PR compared with placebo and PR for 48 weeks. 70.5% of all patients treated with the TT achieved SVR compared to 34.4% in the placebo group (6). Importantly, in this study only treatment-naïve patients were included and less than 10% of patients had advanced fibrosis ( $\geq$  F3). However, patients with advanced fibrosis are at highest risk for decompensated liver disease and hepatocellular carcinoma (HCC) and prompt initiation of treatment is strongly recommended (5). Recently, data in mono-infected patients showed, that in prior non responders a 12 week course of a triple therapy (TT) with telaprevir and PR followed by another 24 weeks of PR resulted in an SVR of only 29% (6, 7). In HCV-HIV co-infected non-responders with unfavourable preconditions (e.g. HCV-genotype 1, interleukin 28 B non-CC genotype, advanced liver fibrosis, high baseline HCV viral load) SVR after TT is even expected to be lower. These patients urgently need additional therapeutic options with the goal to eradicate HCV in order to prevent further fibrosis progression and to reduce morbidity and mortality.

A promising substance in the field of drugs targeting the HCV replication is silibinin. Silibinin is the main component of silymarin, an extract of the milk thistle *Silybum maritimum*. In 2008 Ferenci et al. for the first time reported the substantial clinical antiviral-effect of intravenous silibinin (iSIL) against HCV in PR non-responders. The administration of 20mg/kg iSIL in 20 patients led to a highly significant decrease in viral load (log drop  $3.02 \pm 1.01$ ) (18).

Figure 1: Changes in HCV RNA during IV administration of silibinin at various doses for 14 days, followed by combination therapy with PR, which was started on day 8. Ferenci et al., Gastroenterology, 2008

[figure not shown]

We intend to investigate the effect and tolerability of iSIL in HIV-HCV co-infected individuals with advanced liver fibrosis and previous non- or partial response to SOC.

## 4.2 Investigational Product

Intravenous Silibinin (iSIL) is available on the market in its esterified modification silibinin-C-2, 3-dihydrogen succinate, disodium salt as Legalon® SIL. Legalon® SIL is currently authorized and marketed in Switzerland in the name of Max Zeller Söhne AG, licensee of Madaus GmbH a company of the Rottapharm| Madaus Group (RPH). Legalon® SIL is authorized since the mid-1980 for the treatment of hepatic intoxication with *Amanita phalloides* mushrooms in some EU Member states (e.g. in Germany since 18.04.1984). In Austria, Legalon® SIL is approved since December 2010 for the treatment of chronically infected HCV-patients with non- or partial response to standard therapy with PR. iSIL will be administered intravenously during 2-4 hours.

Intravenous silibinin (iSIL) targets multiple steps in the virus life cycle and exhibits anti-oxidant, anti-inflammatory, anti-viral and immunomodulatory properties (8). iSIL inhibits the HCV NS5B polymerase activity directly or by interfering with the binding of RNA to this enzyme (9). In addition, iSIL appears to block virus entry, virus transmission and virus secretion (10).

### 4.3 Preclinical Data

Detailed information about Non-Clinical studies are provided in the Investigator Brochure, which are briefly summarized hereafter

#### Safety Data:

In the acute test silibinin-C-2', 3-dihydrogen succinate (SHS), disodium salt proved to be practically non-toxic. The LD50 values after intravenous injection may thus be accepted for rats and mice of both sexes as > 1000 mg/kg.

After intravenous, intra-arterial or intramuscular injection a good local tolerance was observed in rats and rabbits.

In a subacute study over 4 weeks, the active ingredient was well tolerated by male and female beagle hounds in the dose range investigated up to 150 mg/kg per infusion – except for a low-grade transient depressant effect on the circulation in the high dosage group.

Toxicological investigations into the reproduction of rats and rabbits did not reveal any embryo-lethal and/or teratogenic effects after doses of up to 50 mg/kg. After the administration of higher doses, fetal death due to maternal toxic effects was recorded.

Mutagenicity tests carried out on microorganisms (Ames test) and mammalian cells in vitro (CHO- and Mouse-Lymphoma Test) did not raise concerns.

In a more recent preclinical toxicity study, a significant and reversible increase in total bilirubin was observed in dogs at toxicological doses (200/400 mg/kg expressed as SHS). No other changes related to liver dysfunction and no abnormal histopathological findings were observed. No signs of cholestasis were detected histologically.

#### Pharmacodynamic properties:

The antiviral effects of SHS were evaluated in a biochemical assay for inhibitors of NS5B RNA-dependent RNA polymerase, in HCV genotype 1a and 1b replicon systems, and in a HCV genotype 2a strain JFH1 cell culture system. These studies showed that SHS is able to inhibit HCV NS5B polymerase function and HCV replication at concentrations that are in the same order of magnitude of the SHS concentration that can be measured in the plasma of HCV patients after intravenous administration of Legalon® SIL at doses equivalent to 20mg silibinin per kg body weight.

score  $\geq 3$ ), an unfavourable interleukin 28 B genotype and a high baseline HCV viral load. The study results confirmed the efficacy of iSIL in a difficult-to treat patient group and underscored that iSIL could be a valuable treatment-option in patients not responding to PR (12). The potential role of iSIL as rescue therapy in patients not responding to previous combined therapy with PR and a HCV-specific PI was demonstrated by Biermer et al., 9 of the 13 responder patients are in the follow-up period: 3 of them achieved SVR24, 2 achieved SVR12, and 4 had a viral relapse (13). Recent reports also show the efficacy of iSIL in patients with HCV-reinfection after liver transplantation. After 14 days treatment of iSIL in a dosage of 20mg/kg all four patients showed normalization of liver enzymes and a significant decline of HCV-RNA with a mean log-reduction of 2.8 (14). Moreno et al. presented their data about the safety and the anti-HCV activity of a rescue therapy with iSIL in cirrhotic HIV-HCV co-infected individuals at the 19th conference on retroviruses and opportunistic infections (CROI) in 2012. They treated 4 individuals with previous partial response (PR) or relapses to PR with iSIL 20mg/kg for at least 14 days. Three patients started iSIL during PR and nitazoxanide (add-on strategy). Overall, therapy with iSIL led to negative HCV-RNA in 3 subjects and values  $<50$  IU/mL in the remaining. The period of mono-therapy with iSIL produced a time-dependent effect: the mean decrease of HCV-RNA was  $-2.5 \log_{10}$  IU/ml after 1 week and  $-4.62 \log_{10}$  IU/ml after 35 days. However, HCV-RNA rebounded in 4 patients after stopping iSIL. There were no significant adverse events related to iSIL and all patients maintained current antiretroviral therapy (ART) with undetectable HIV RNA (15).

#### **4.5 Dose Rationale**

All included study-subjects will receive a lead-in therapy with iSIL in a dosage of 20mg/kg/day (expressed as silibinin concentration) once a day for 14 days. At the end of the THISTLE study, i.e. after the day of completion of the 14-day iSIL administration (day 15), the patients will be considered for eligibility to receive standard of care TT with telaprevir (i.e. 12 weeks combination therapy with telaprevir plus PR followed by 36 weeks of PR).

The rationale of 20mg/Kg/day is the observation, that there exist a strong dose-dependent effect with a greatest HCV-RNA decline when iSIL is administrated in a dose of 20mg/kg, whereas the lower dose (5, 10 or 15mg/kg) led to a significant lower HCV-RNA decline (16). iSIL dose-dependently reduced and even completely eradicated the HCV load, with the dose of 20 mg/kg per day being clearly the most effective dose.

Since effective antiviral concentration cannot be reached with the oral administration with the available formulations of silymarin/silibinin, the drug needs to be administrated intravenously. The rationale to use 14 days of treatment is a trade-off between virological efficacy of this treatment and logistic and financial constraints. Previous reports (10, 16) demonstrated a continuous decline during 2 weeks of iSIL therapy with a mean decline of 3 logs IU/ml in HCV-RNA. We assume that this decline would substantially improve the chances of SVR as this reduction of viral load should both increase the efficacy of PR and reduce the odds of drug resistance to telaprevir.

#### **4.6 Risk/Benefits and Ethical Considerations**

The study has not been designed as placebo-controlled study because of ethical considerations. A placebo-controlled study was extensively discussed in our scientific-

group, within SHCS and also representatives of the ethical committee of the University of Zurich. On the background of the urgent need of a new treatment strategy for this selected difficult to treat patient population together with the apparently excellent tolerability of iSIL, it was considered ethically not justifiable to withhold the lead-in treatment with iSIL, and as a consequence it was decided to offer all patients the chance to receive an active treatment since a standard rescue strategy is not available for the treatment of patients with incomplete virological response.

In addition, the expected benefits of iSIL justify the risks, which possibly arise from the administration of the study medication. Details about the risks associated with iSIL administration have been provided in Section 10.6. Basically this study is considered to be a phase II trial with focus to safety and tolerability.

## **5 STUDY OBJECTIVES AND OUTCOMES**

### **5.1 Primary Variable(s)**

#### ***Primary aims***

The aim of this study is to evaluate the safety and efficacy of a 14 days lead-in course with iSIL in HCV-HIV co-infected individuals who failed previous treatment with PR.

- To assess the safety of iSIL in the context of HCV-HIV co-infected patients and HIV antiretroviral treatment (ART).
- To evaluate the kinetics of the decline in HCV RNA from baseline after 2 weeks of iSIL treatment

#### ***Primary endpoints:***

- Frequency of adverse events during iSIL treatment.
- Kinetics of the decline in HCV-RNA after 2 weeks of iSIL treatment (difference in IU/ml from day 1 to day 15, see flow-chart below).

### **5.2 Secondary Variables**

#### ***Secondary aims***

- To assess the efficacy of iSIL in a variety of clinically meaningful virological responses
- To evaluate drug levels of iSIL and to assess its influence on the drug-levels of co-administrated ART.

#### ***Secondary endpoints:***

- Drug levels of iSIL and its influence on the drug-level of co-administrated ART.
- Proportion of patients with HIV virological failure, i.e. confirmed viremia >50cp/ml.

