## 6 STUDY DESIGN AND COURSE OF STUDY

### 6.1 General Design

This study is a multicentre, open-label, interventional study including HCV-HIV co-infected individuals with chronic HCV-genotype 1 infection and documented previous null-response (NR) or partial-response (paR) to standard therapy with SOC and progressed liver fibrosis.

The overall study-duration is 15 days. The first part is the once a day administration of iSIL from day 1 to 14. Since the half-life ( $T_{1/2}$ ) of the administrated study-drug is very short (3 hours), the follow-up of the study-subjects is one day (day 15) and the final visit will be on day 15.

Subsequent to THISTLE (at day 15) we have the intention to include the study-subjects in the SHCS trial # 688. The trial # 688 will investigate the occurrence of HCV-resistance to the HCV-PIs during TT. The duration of the # 688 will contain 48 weeks with a follow-up of 24 weeks. Importantly, we plan to review the results from the THISTLE trial with the data from the SHCS # 688.

The estimated time frame is listed below:

- Submission to ethical committee (Zurich as lead ethical committee): November 2012
- Ethical approval: January 2013
- Swissmedic approval: February 2013
- First patient enrolled: April 2013
- Enrolment: April 2013 to December 2013
- Last patient enrolled: End of December 2013

All included patients will receive a lead-in therapy with iSIL in a dosage of 20mg/kg/day for 14 days followed by standard of care TT. As mentioned above, the follow-up period will contain for one day due to short half-life time of the administrated study-drug. Moreover, a prolonged follow-up period outside THISTLE trial is warranted due to the SHCS trial # 688.

The included patients are HCV-HIV co-infected SHCS participants with chronic HCV-genotype 1 infection and documented previous null-response (NR) or partial-response (paR) to standard therapy with SOC and in urgent need of treatment (i.e. METAVIR fibrosis score  $\geq 2$  or ISHAK fibrosis score  $\geq 4$  or fibroscan stiffness  $\geq 9.5$  kPa). As cut-offs for the fibroscan we used the ones proposed in a recent review by Castera et al (17). NR is defined as less than 2 log10 IU/ml decrease in HCV RNA level from baseline at 12 weeks. paR is defined as more than 2 log10 IU/ml decrease in HCV-RNA level from baseline at 12 weeks of therapy but detectable HCV-RNA at weeks 12 and 24.

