#### Exclusion criteria:

- contraindications to the study drug under study, e.g. known hypersensitivity or allergy to any ingredient of the study drug,
- women who are pregnant or breast feeding,
- intention to become pregnant during the course of the study,
- lack of safe contraception, defined as:  
Female subjects of childbearing potential, not using and not willing to continue using a medically reliable method of contraception for the entire study duration, such as oral, injectable, or implantable contraceptives, or intrauterine contraceptive devices,

or who are not using any other method considered sufficiently reliable by the investigator in individual cases.

Please note that female subjects who are surgically sterilized/hysterectomized or post-menopausal for longer than 2 years are not considered as being of child bearing potential.

- Male patients who do not agree to abstain from intercourse or who do not use a condom
- other clinically significant concomitant unstable disease states (e.g., renal failure, unstable cardiovascular disease),
- known or suspected non-compliance, drug or alcohol abuse,
- inability to follow the procedures of the study, e.g. due to language problems, psychological disorders, dementia, etc. of the subject,
- participation in another study with investigational drug within the 30 days preceding and during the present study,
- previous enrolment into the current study,
- enrolment of the investigator, his/her family members, employees and other dependent persons
- Patients in need of ART with HIV virological failure ( $\geq 400$  copies/ml) in the last 3 months
- Any other condition that, in the opinion of the Investigator, may jeopardize the study conduct according to the protocol.

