## **9 STUDY PROCEDURES**

### **9.1 Day – 14 (Screening visit)**

- Information of patient and Informed Consent
- Check for inclusion and exclusion criteria
- Medical History and prior concomitant medication
- Physical Examination:
  - Including blood pressure while sitting (right/left), pulse rate, temperature (degree Celsius), cardiac auscultation, chest auscultation, abdominal auscultation, brief neurological examination
- Concomitant medication
- Pregnancy test:
  - 10ml Heparin blood
- HCV-RNA, HIV-RNA
  - 10ml EDTA blood
- Full blood count, electrolytes (sodium, potassium), ASAT, ALAT, total and fractionated bilirubin, alkaline phosphatase, gammaGT, creatinine, albumin, total protein, INR, thyroid stimulating hormone (TSH)
  - 10ml Heparin blood
- Interleukin 28B genotype (if not available):
  - 10ml EDTA blood
- Plasma aliquot as backup-blood for potential later analysis
  - 10ml EDTA blood
- Accepted time window:  $\pm 3$  days

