### **9.2 Day + 1 (baseline visit), immediately previous to iSIL administration**

- Check for inclusion and exclusion criteria
- Documentation of adverse events
- Concomitant medication
- Physical examination
  - Including blood pressure while sitting (right/left), pulse rate, temperature (degree Celsius), cardiac auscultation, chest auscultation, abdominal auscultation, brief neurological examination

- Safety laboratory: full blood count, electrolytes (sodium, potassium), ASAT, ALAT, total and fractionated bilirubin, gammaGT, total protein, alkaline phosphatase, creatinine, albumin, INR
  - 10ml Heparin blood
- HCV-RNA, HIV-RNA
  - 10ml EDTA blood
- CD3/4/8 count
  - 3ml EDTA blood
- Drug level of current ART
  - 10ml EDTA blood
  - Note the time-point (date, hour, minutes) of the last intake and the dosage (milligram) on the electronic CRF
  - Blood (10 ml) must be collected in EDTA solution vacutainer tubes. The tubes containing EDTA solution should be stored at +4°C. Tubes must be identified with the patient ID number and sample number as soon as blood has been collected
  - Blood samples must be brought to the laboratories without delay (maximum 30 min after blood collection).
  - Treatment of samples: centrifugation at 1500g for 10 min at +4°C. In a class II biohazard hood plasma (obtained after centrifugation) should be divided in three labelled tubes (of approximately 1mL each) ready for freezing at -80 ° C, within one hour after collection. If this deadline cannot be met, please keep the sample at 4° C until centrifugation and freezing
- Silibinin drug-level (Cmin (T0, pre-dose), Cmax (i.e immediately after the end of silibinin infusion) and one sampling at T4 (i.e. 4 hour after the end of silibinin infusion)
  - Blood (6 ml) must be collected in ACD (acid citrate dextrose) solution vacutainer tubes. The tubes containing ACD solution should be stored at +4°C. Tubes must be identified with the patient ID number and sample number as soon as blood has been collected
  - Blood samples must be brought to the laboratories without delay (maximum 30 min after blood collection).
  - Treatment of samples: centrifugation at 1500g for 10 min at +4°C. In a class II biohazard hood plasma (obtained after centrifugation) should be divided in three labelled tubes (of approximately 1mL each) ready for freezing at -80 ° C, within one hour after collection. If this deadline cannot be met, please keep the sample at 4° C until centrifugation and freezing.

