### 9.16 Day 15 (visit 16, end of THISTLE)

- Documentation of adverse events
  - use the electronic CRF
- Concomitant medication
  - use the electronic CRF
- Physical examination
  - Including blood pressure while sitting (right/left), pulse rate, temperature (degree Celsius), cardiac auscultation, chest auscultation, abdominal auscultation, brief neurological examination
- Safety laboratory: full blood count, electrolytes (sodium, potassium), ASAT, ALAT, total and fractionated bilirubin, gamma GT, alkaline phosphatase, creatinine, albumin, total protein, INR
  - 10ml Heparin blood
- Pregnancy test:
  - 10ml Heparin blood
- HCV-RNA, HIV-RNA
  - 10ml EDTA blood
- CD3/4/8 count
  - 3ml EDTA blood
- Plasma aliquot as backup-blood for potential later analysis
  - 10ml EDTA blood
- PBMC: only at the study site Zurich
- Silibinin drug-level T24 (i.e 24 hour after the end of last silibinin infusion)
  - Blood (6 ml) must be collected in ACD (acid citrate dextrose) solution vacutainer tubes. The tubes containing ACD solution should be stored at +4°C. Tubes must be identified with the patient ID number and sample number as soon as blood has been collected
  - Blood samples must be brought to the laboratories without delay (maximum 30 min after blood collection).
  - Treatment of samples: centrifugation at 1500g for 10 min at +4°C. In a class II biohazard hood plasma (obtained after centrifugation) should be divided in three labelled tubes (of approximately 1mL each) ready for freezing at -80 ° C, within one hour after collection. If this deadline cannot be met, please keep the sample at 4° C until centrifugation and freezing.
- Accepted time window: at least one day after the end of iSIL administration

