#### Plasma aliquots:

- Two aliquots of EDTA plasma samples will be obtained at each study site on the screening visit, visit 1, 8, 12, 15. The aliquots will be used as backup-blood for potential later analysis. The aliquots should contain at least 5 mL plasma. The plasma samples will be stored at -20°C or colder.
- The plasma aliquots will be stored for 5 years in accordance to the biobank-protocol if a separate informed consent form was obtained.

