## 10.7 Assessment of safety laboratory parameters

The laboratory tests listed in Table below will be performed at the laboratory of each study site and the laboratory of [name] in Lausanne. For time points of laboratory sampling refer to the Flow Chart. Laboratory results of the patients will be available to the investigator of each study site and selected abnormal laboratory alerts will be sent automatically to the sponsor within 24 hours. Clinically relevant laboratory values should be commented on lab report print-outs. A clinically relevant value may be either in- or outside the reference range. Out-of-range data judged as clinically significant (CS) by the Investigator has to be report as an adverse event. Clinically relevant abnormal laboratory test results must be confirmed and should be repeated until normalization or stabilization or until an alternative explanation has been found.

| Category             | Test name                                                                                                                                                                                                                                                                                                               |
|----------------------|-------------------------------------------------------------------------------------------------------------------------------------------------------------------------------------------------------------------------------------------------------------------------------------------------------------------------|
| Haematology          | Hematocrit (Hct)
Hemoglobin (Hb)
Red Blood Cell Count/ Erythrocytes
White Blood Cells / Leukocytes
Platelet Count/ Thrombocytes
Diff. Automatic Neutrophils (relative count)
Eosinophils (relative count)
Basophils (relative count)
Monocytes (relative count)
Lymphocytes (relative count) |
| Coagulation          | Prothrombin time (Quick and INR)                                                                                                                                                                                                                                                                                        |

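### The confirmed HIV viraemia endpoint does not fit the schedule: HIV-RNA is taken once after iSIL starts, at the final visit, with no confirmatory sample scheduled and no baseline condition

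*Protocol*

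**What the plan says.** Section 5.2 and the synopsis give as a secondary endpoint "Proportion of patients with HIV virological failure, i.e. confirmed viremia >50cp/ml". Neither says what counts as confirmation (how many samples, how far apart), and neither sets a starting condition on HIV-RNA.

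The schedule table and the visit lists in section 9 agree on when HIV-RNA is drawn:

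- **Screening (9.1):** "HCV-RNA, HIV-RNA".
- **Day 1 (9.2):** the visit is placed "immediately previous to iSIL administration", so this sample is also pre-dose.
- **Days 2 to 14 (9.3 to 9.15):** HCV-RNA only.
- **Day 15 (9.16):** HIV-RNA again. The window is "Accepted time window: at least one day after the end of iSIL administration". It has no upper limit but still yields one sample.

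Section 6.1 states that "the follow-up of the study-subjects is one day (day 15) and the final visit will be on day 15".

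The only limit on HIV viraemia at entry is the exclusion in 7.2 of "Patients in need of ART with HIV virological failure" at 400 copies/ml or more in the last 3 months.

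Two general safety rules also bear on the point. Section 10.7 says "Clinically relevant abnormal laboratory test results must be confirmed and should be repeated until normalization or stabilization", and its table of tests includes plasma HIV RNA. Section 10.5 provides a visit up to 30 days after treatment for ongoing SAEs, or for ongoing AEs of laboratory values or vital signs beyond the alert limit.

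**The concern.** Confirming a new rise in HIV-RNA takes a raised value and a second raised value after it. For viraemia that emerges under iSIL, the schedule can supply only the first, and it does so on the day the study ends.

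The wording also lets in viraemia that predates the drug. Patients on ART with 51 to 399 cp/ml, or patients not in need of ART, pass the 7.2 criterion and may already be above 50 cp/ml before the first infusion.

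This is the only listed endpoint that measures HIV control directly, and a primary aim is to assess the safety of iSIL in patients with HIV and ART. Applied literally to the scheduled data, the endpoint misses the events of interest and can count events that are not of interest. A low proportion could be taken as reassurance about iSIL and a raised one as a signal, and neither reading would be sound. The sensitivity analyses in 12.3 do not help: for a day-15 value above 50 cp/ml with no repeat, the missing=failure or missing=success rule would itself decide the result.

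**Working it through.** The protocol states no expected rate or precision for this endpoint, so there is no figure to reproduce.

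**Inputs.** Scheduled HIV-RNA samples: 3 (schedule table; 9.1, 9.2, 9.16). Of these, 2 are pre-dose and 1 is post-dose. Planned subjects: 20 (12.4). Assumption: 'confirmed' means two consecutive samples above 50 cp/ml.

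**Step 1: which patterns can meet the endpoint.** Three samples, each above 50 or not, give 2 × 2 × 2 = 8 patterns.

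| Screening | Day 1 | Day 15 | Confirmed? | New on iSIL? |
|---|---|---|---|---|
| ≤50 | ≤50 | ≤50 | no | no |
| ≤50 | ≤50 | >50 | no | **yes** |
| ≤50 | >50 | ≤50 | no | no |
| ≤50 | >50 | >50 | yes | no |
| >50 | ≤50 | ≤50 | no | no |
| >50 | ≤50 | >50 | no | no |
| >50 | >50 | ≤50 | yes | no |
| >50 | >50 | >50 | yes | no |

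The one pattern that is a new failure cannot be confirmed. The three that are confirmed all include a pre-dose value above 50 cp/ml. Dropping the word 'consecutive' adds only the pattern >50, ≤50, >50 and changes nothing else: with one post-dose sample, any two of the three must include a pre-dose one.

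**Step 2: what scheduled data would report for new failures.** The count is 0/20 whatever the true rate. The exact (Clopper-Pearson) upper 95% limit is 1 − 0.025^(1/20) = 0.168, so the result would read 0% (0% to 16.8%).

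**Step 3: what would be left out.** Let p be the true proportion newly above 50 cp/ml on day 15. The protocol gives no value, so p is assumed over a range. The chance that at least one of 20 patients shows such a value is 1 − (1 − p)^20:

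- p = 5%: 1 − 0.95^20 = 64%
- p = 10%: 1 − 0.90^20 = 88%
- p = 15%: 1 − 0.85^20 = 96%

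None of these patients would count as confirmed on scheduled samples.

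**Step 4: viraemia present before treatment.** Each patient with one of the three confirmed patterns adds 1/20 = 5 percentage points. The number of such patients cannot be derived from the protocol.

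**The case against.** A reader might infer that the endpoint can never be observed and is 0% by construction. The documents do not support that. Section 10.7 lists HIV-RNA among the tests whose clinically relevant abnormal results must be confirmed and repeated, and section 10.5 allows a later visit under stated conditions. A raised day-15 value could therefore be repeated. These routes do not repair the endpoint: neither names it, sets a trigger at 50 cp/ml or gives a time for the repeat. The repeat also rests on the investigator's judgement. With triple therapy planned from day 15, it would probably not reflect iSIL alone. The zero result therefore holds for scheduled samples only.

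A reader might also infer that every patient viraemic at entry inflates the result by 5 points. That goes too far. It takes two raised values, and it takes a reading of virological failure that includes patients off ART or with low-level viraemia. The other use of the term, in 7.2, is confined to patients in need of ART, and the number of such entrants is unknown.

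It is fair to say, too, that a statistical analysis plan could define confirmation and the denominator. It could not add a sample that the protocol does not schedule.

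Finally, the endpoint is secondary, section 12.1 calls the analysis purely descriptive, and no sample size or decision rule depends on it. The day-15 value is collected and can be reported whatever it is called, and ART drug levels on days 1 and 12 address interaction separately. All of this limits the severity. It does not make the endpoint fit its schedule.

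**Conclusion.** The point holds for the scheduled data. With one HIV-RNA sample after iSIL starts, a new failure cannot be confirmed on schedule: new confirmed failures would be 0/20 (95% CI 0% to 16.8%) at any true rate. Only patients with a pre-dose value above 50 cp/ml can meet the definition on scheduled samples, each adding up to 5 percentage points that say nothing about iSIL.

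This rests on reading 'confirmed' as two raised samples, on 20 patients with all three values, and on no unscheduled repeat. An unscheduled repeat could lift the count above zero, but the protocol does not link one to this endpoint.

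Severity is moderate. The proportion as defined would be uninformative or misleading, but no primary result depends on it and the data for a sound definition are already collected.

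**What to change.** Redefine the endpoint in 5.2 and the synopsis, and state its analysis in 12.1, as the proportion with a single HIV-RNA above 50 cp/ml on day 15, among patients on ART whose HIV-RNA was at or below 50 cp/ml at both screening and day 1.

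- **Supportive information only:** test stored plasma from day 12 where biobank consent exists. Section 9.17 provides that "Two aliquots of EDTA plasma samples will be obtained at each study site on the screening visit, visit 1, 8, 12, 15"; the numbers read as study days, and 9.13 lists the aliquot on day 12. It is taken on iSIL and before triple therapy, but it misses viraemia that first emerges after day 12.
- **Later values:** do not use HIV-RNA from SHCS trial #688 or routine care after day 15 as evidence about iSIL alone, because triple therapy is planned from that day.
- **Other patients:** report those off ART, or above 50 cp/ml at entry, separately as log10 change in HIV-RNA from day 1 to day 15.

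The cost is a rewording and, optionally, a few assays on stored plasma. No visit or treatment rule changes. There are two drawbacks. Isolated single-value blips will count as events. The denominator shrinks somewhat: for illustration, the upper limit for zero events moves from 16.8% with 20 patients to 1 − 0.025^(1/18) = 18.5% with 18.
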